## **10. PCR for recurrent parasitaemia**

Blood for PCR will be collected from all patients at enrolment and on the day of re-appearance of parasitaemia. PCR analysis of parasite genes will be performed only in patients with re-appearance of parasitaemia in order to differentiate between re-infection and recrudescence. Blood spots will be collected on glass fibre membranes and DNA extracted using standard techniques. The polymorphic repetitive regions to be amplified by nested-PCR are block 2 of *msp1* and block 3 of *msp2* (Snounou *et al*, 1993). In a first reaction, polymorphic sequences of these genes will be amplified using primer pairs to their conserved regions. Using the template of the first PCR reaction, allele-specific primer pairs will be used to test for the presence of the allelic variants from the MAD20, RO33 and K1 families of the *msp1* and FC27 and 3D7/IC of the families of the *msp2*. PCR products will be analysed by gel electrophoresis. Amplification patterns of the various allelic families in DNA samples from day 0 will be compared to other samples from the same patient who was parasitaemic on or after day 14 post-treatment. If the allelic family (ies) amplified on day 0 are identical in size to those amplified from subsequent episode, then the patient is classified as carrying a recrudescence infection. If however the pattern of amplification is different for any allelic family, then it is assumed that this is a new infection.

## **11. Data analysis.**

The primary outcome will be by treatment defined as having at least one dose of study drug. A secondary analysis will be by intention to treat defined as being enrolled into the treatment log and assigned a number. Treatment failure as defined in section 4.1 is the primary outcome.

Other pre-planned analyses are:

- Fetal viability;
- Birth outcome 6 weeks after due date;
- Parasite clearance rate at day 3;
- Parasite recrudescence or reinfection rate by day 14;
- Fever clearance rate (time);
- Level of recovery of Hb on day 14;
- Adverse events;
- Relapse confirmed by PCR.

Planned stratified analyses are by parity and HIV serostatus.

## **12 Capacity strengthening.**

Provisional plans for capacity strengthening locally have been discussed with the Acting Medical Superintendent, Teule Hospital, and the Director, NIMR-Amani. Provisional plans include the following (this is not an exhaustive list).

Building and equipping of a ward at Teule Hospital. The ward will be potentially multi-use, and can be used for clinical studies or patient use for pregnant mothers or children. This ward has been considered by the Board of Governors of Teule Hospital, and they consider it very desirable for their long-term needs if there is a period it is not necessary for clinical studies.

Training in clinical trials for Hospital staff and the possibility of secondments for NIMR clinical staff.

Teaching ward rounds and clinical involvement in the hospital by senior trial staff.

Training in PCR for NIMR staff, either locally or in London depending on what is appropriate.

Training in clinical chemistry for laboratory technicians.

Improved clinical laboratory infrastructure.

A clinical platform for pharmacological and immunological studies by NIMR and LSHTM staff.

## **ETHICAL ISSUES**

### **Discuss ethical aspects of the proposal.**

#### **1) Approval by the local Institutional Review Board (IRB) or Ethical Committee (IEC)**

This protocol was submitted to Ethical Committees of the National Institute for Medical Research in Tanzania and has been approved. It has been submitted to the London School of Hygiene and Tropical Medicine Ethics Committee and has been approved.

#### **2) Subject information and Informed Consent**

- a) Each woman will receive written information (in Kiswahili) about the study, which will also be explained in the presence of the witness when applicable. Sufficient time will be allowed for the woman to decide if she wishes to join the study;
- b) Women will be allowed to enquire about details of the study and any question regarding the study will be answered;
- c) The PI will ensure that the consent form has been signed and dated by the participant, attending clinician and/or witness where applicable;
- d) In the case of a patient who cannot read, an independent literate witness will attend the information session, sign and date the consent form on behalf of the patient;
- e) In case of protocol amendments, the PI will ensure that the consent form is also revised to reflect the approved amendments.

3) All drugs used in the study have been used for treating malaria in pregnancy previously (see section 6.1 for further details), although not necessarily in the combinations proposed in this study.

4) An independent Data and Safety Monitoring Board (DSMB) will be set up. This will receive reports of all adverse events, and of treatment failures to ensure it is safe to continue the trial. Exact terms of reference and provisional stopping rules will be determined in consultations between the Committee and the trial investigators.

#### **5) This study will contribute to capacity strengthening;**

- a) through improved infrastructure at Teule hospital (deemed appropriate with authorisation given by the Governors of the Hospital and by the Ministry of Health);
- b) through provision of additional clinical services and training within the hospital for the duration of the study;
- c) provision of an infrastructure that can support additional projects.

## Appendix 1

**Drug administration and collection of monitoring variables of mother**

## Time and events schedule

| Study Day                                         | Treatment with study drugs  |                |                | Follow-up through D 28 |    |    |    | At delivery | At the time of treatment failure |
|---------------------------------------------------|-----------------------------|----------------|----------------|------------------------|----|----|----|-------------|----------------------------------|
|                                                   | 0
Screening/
Baseline | 1              | 2              | 7                      | 14 | 21 | 28 |             |                                  |
| Written Informed Consent                          | ✓                           |                |                |                        |    |    |    |             |                                  |
| Inclusion/Exclusion Criteria                      | ✓                           |                |                |                        |    |    |    |             |                                  |
| Demography                                        | ✓                           |                |                |                        |    |    |    |             |                                  |
| Medical History                                   | ✓                           |                |                |                        |    |    |    |             |                                  |
| Physical Examination                              | ✓                           | ✓              | ✓              | ✓                      | ✓  | ✓  | ✓  | ✓           | ✓                                |
| Fetal viability                                   | ✓                           | ✓              | ✓              | ✓                      | ✓  | ✓  | ✓  |             | ✓                                |
| Vital Signs (BP, PR, RR)
Temperature           | ✓ a              | ✓ a | ✓ a | ✓                      | ✓  | ✓  | ✓  | ✓           | ✓                                |
| Assessment of Clinical Symptoms of Malaria        | ✓                           | ✓              | ✓              | ✓                      | ✓  | ✓  | ✓  | ✓           | ✓                                |
| Adverse Event Review                              | ✓                           | ✓              | ✓              | ✓                      | ✓  | ✓  | ✓  | ✓           |                                  |
| Concurrent Medication Review                      | ✓                           | ✓              | ✓              | ✓                      | ✓  | ✓  | ✓  | ✓           |                                  |
| Malaria Finger-prick blood smears                 | ✓ b              | ✓ b | ✓ b | ✓                      | ✓  | ✓  | ✓  | ✓           | ✓                                |
| Blood Sample for Parasite DNA                     | ✓                           |                |                |                        |    |    |    |             | ✓                                |
| HIV test                                          | ✓                           |                |                |                        |    |    |    |             |                                  |
| Clinical Chemistry                                | ✓                           |                |                | ✓ c         |    |    |    |             |                                  |
| Haematology                                       | ✓                           |                |                | ✓                      |    |    |    |             |                                  |
| Routine urinalyses                                | ✓                           |                |                | ✓                      |    |    |    |             |                                  |
| Treatment with study drug                         | ✓                           | ✓              | ✓              |                        |    |    |    |             |                                  |
| Placental and Newborn investigations d |                             |                |                |                        |    |    |    | ✓           |                                  |
| Assessment of new-born e               |                             |                |                |                        |    |    |    |             |                                  |

a. Temperature to be monitored every 12 hours until the temperature falls below 37.5 °C and remains normal for at least 24 hours.

b. Blood smear done once daily during hospitalization, at follow up visits, and at any time of complaint of fever.

c. If abnormal, follow up assessment will be done once weekly until the values are normal.

d. Placental blood smear, cord blood smear, newborns weight (kg), and Dubowitz assessment if day 28 is around delivery time.

e. Weight and maturity assessment if day 28 is around delivery and women delivers at hospital (study site)

**Note:** BP = blood pressure, PR = pulse rate, RR = respiratory rate

Monitoring of child at birth and one month is outlined in the text.

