## **4.2 Secondary endpoints**

Secondary endpoints will include the following:-

1. Incidence of foetal death during treatment, defined as absence of foetal heartbeat assessed by Doppler;
2. Hypoglycaemia requiring treatment;
3. Parasite recrudescence or re-infection on day 14;
4. Parasite clearance on day 3;
5. Level of recovery of haemoglobin on day 14;
6. Fever clearance time;
7. Incidence of perinatal and neonatal mortality, assessed 4-6 weeks after due date of delivery;
8. Clinically apparent neonatal abnormality, assessed 4-6 weeks after due date of delivery;
9. Placental malaria
10. Preterm delivery
11. Other adverse events during treatment.

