### **5.2 Inclusion criteria**

A pregnant woman who has:-

*either* a positive blood smear for *P.falciparum* with at least 1000 asexual parasites/ $\mu$ L in an asymptomatic woman  
*or* any of the following symptoms within 2 days prior to consultation: history of fever; headache, vomiting, chills/rigors, and/or any of the following signs: temperature  $\geq 37.5^{\circ}\text{C}$  and  $< 39.5^{\circ}\text{C}$ , Hb  $\geq 5$  and  $< 9$  g/dl) together with *P.falciparum* parasitaemia at any density

and (in both cases) the following:

1. has no exclusion criterion (see below);
2. is 14-34 weeks pregnant on the day of attending the ANC clinic or OPD;
3. has a viable foetus, defined by presence of foetal heartbeat by sonicaid or pinnard (foetal heartbeat is not heard until 14 weeks);
4. is able to take study drugs by the oral route;
5. is able to attend stipulated days for follow up clinic and provide specimens;
6. gives informed written or witnessed verbal consent to participate by herself, and also through her parent/guardian if aged  $< 15$  years (in conformity to Tanzania Law).

Those  $> 34$  weeks are excluded because they are close to term and may deliver during the 28 day f/u period.

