## **6.3 Clinical treatment and investigations.**

All women enrolled will be admitted to the research ward (to be built by the GMP) for the first three days for DOT and to monitor clinical response and adverse events. Drugs will be administered by nurses employed by the project. After each administration, the patient will be observed for 45-60 minutes to ascertain drug retention. The dose will be repeated if vomiting occurs within the observation period, and any further vomiting will cause withdrawal from the study and treatment with parenteral quinine. Patients will be treated for symptoms by standard treatment e.g. paracetamol for fever. Women will also continue to receive routine antenatal medicaments of iron supplements, folic acid, and Tetanus Toxoid (TT) given by the MCH. Drugs with an antimalarial activity will not be permitted; if these are essential, the subject will be withdrawn.

Vital signs (temperature, pulse) will be monitored eight hourly during the treatment period and once daily during the remaining period of hospitalisation. Blood pressure will be measured once daily during hospitalisation. Patients will be interviewed using a “clinical assessment form” check list which includes: weakness, chills/rigors, headache, myalgia, dizziness, abdominal pain, anorexia, nausea, vomiting, diarrhoea, palpitations, insomnia, pruritus, coughing, and tinnitus. Blood glucose will be measured on admission and regularly through treatment by glucose stix testing.

Foetal viability (presence of foetal heartbeat) will be monitored daily during admission using a Doppler machine, and at each follow-up visit.

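### Placental malaria is a secondary endpoint, but the placental smear is planned only when delivery falls near day 28, which the 34-week entry limit is meant to prevent

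*Protocol*

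**What the plan says.** Section 4.2 lists "Placental malaria" as secondary endpoint 9 and "Preterm delivery" as endpoint 10. Birth outcome is one of the trial's aims in the Summary.

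In the Appendix 1 schedule, the row for placental and newborn investigations is ticked in the delivery column and carries footnote d: "Placental blood smear, cord blood smear, newborns weight (kg), and Dubowitz assessment if day 28 is around delivery time". Footnote e, on assessment of the newborn, reads "Weight and maturity assessment if day 28 is around delivery and women delivers at hospital (study site".

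Section 5.2 admits a woman who "is 14-34 weeks pregnant on the day of attending the ANC clinic or OPD". Later gestations are "excluded because they are close to term and may deliver during the 28 day f/u period".

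The Appendix refers to the text for monitoring of the child. Section 7 (follow-up at birth), item (a), covers deaths, maternal complications and visible abnormalities for women who deliver at the study hospital, put at 70 to 80% of antenatal attenders. It lists no placental smear, newborn weight or maturity score. The maternal finger-prick smear is also scheduled at delivery, but that is peripheral blood.

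On foetal loss, endpoint 1 is "Incidence of foetal death during treatment, defined as absence of foetal heartbeat assessed by Doppler", while section 6.3 has viability "monitored daily during admission using a Doppler machine, and at each follow-up visit".

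**The concern.** The condition in footnote d and the entry rule in section 5.2 work against each other. The first collects placental data only from women who deliver near day 28. The second is there so that women do not deliver in that period. Staff who follow the schedule as printed would skip the placental smear for most women, and a placenta not sampled at delivery cannot be sampled later.

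Two things are at stake for endpoint 9. There would be too few observations to describe an arm, let alone compare arms. Those few would also be chosen by when the woman delivered. That is known only after randomisation and may be affected by treatment, so a comparison between arms in that subset would no longer be a randomised one.

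The Dubowitz score, which would support endpoint 10, carries the same restriction.

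**Working it through.** **Denominator.** The October 2004 revision in the sample size section gives 72 per arm, for day-28 failure of 1% against 15%. I read its β of 0.8 as power.

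- Without continuity correction: n = [1.960·√(2·0.08·0.92) + 0.842·√(0.01·0.99 + 0.15·0.85)]² / 0.14² = 57.75.
- With continuity correction: (57.75/4)·[1 + √(1 + 4/(57.75·0.14))]² = 71.3, so 72.

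The stated figure is reproduced. It serves here only as a denominator, because no sample size is stated for placental malaria or preterm delivery.

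**Where day 28 falls.** Entry at 14 to 34 weeks plus 4 weeks gives 18 to 38 weeks. With a due date at 40 weeks (assumption), a woman enrolled at 34 weeks is 2 weeks from her due date on day 28, and one enrolled at 14 weeks is 22 weeks from it.

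**Share of women delivering within w weeks of day 28.** These assumptions are not in the protocol:

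- Entry gestation is uniform over 14 to 34 weeks.
- Delivery is Normal with mean 39.5 weeks and SD s = 1.5 to 2.5.
- w is 1 to 4 weeks, because the footnote gives no window.
- Preterm means before 37 weeks, because the protocol gives no definition.

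With g(z) = zΦ(z) + φ(z), the share is

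(s/20)·[g((38 − 39.5 + w)/s) − g((38 − 39.5 − w)/s)].

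Example with w = 2 and s = 2: (2/20)·[g(0.25) − g(−1.75)] = 0.1·[0.536 − 0.016] = 5.2%. A simulation under the same assumptions also gave 5.2%.

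Counts per arm are 72 × share × 0.70 to 0.80.

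| Window w (weeks) | Share of women | Hospital deliveries per arm of 72 | Preterm among them |
|---|---|---|---|
| 1 | 1.7-2.8% | 0.9-1.6 | 27-57% |
| 2 | 4.4-5.9% | 2.2-3.4 | 19-51% |
| 3 | 8.1-9.4% | 4.1-5.4 | 14-43% |
| 4 | 12.7-13.5% | 6.4-7.8 | 11-37% |

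Ranges run over the three SDs tried (1.5, 2 and 2.5).

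**Comparison.** Sampling every hospital delivery gives 72 × 0.70 = 50 to 72 × 0.80 = 58 women per arm. The preterm share among all women under the same assumptions is Φ((37 − 39.5)/s), or 5% to 16%. At each SD the near-day-28 subset has a higher preterm share than the whole group.

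**Sensitivity.** If 34 weeks means up to 34 weeks and 6 days, the simulated share is 3.6-17% for windows of 1 to 4 weeks, or about 2 to 10 women per arm. The conclusion does not change.

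**The case against.** The best defence is that footnote d is ambiguous. The table ticks placental and newborn investigations at delivery, and the closing condition could belong to the Dubowitz score alone. Section 7(a) is also worded as a list of inclusions, so its silence does not forbid a smear. This reading is possible but strained. Footnote e puts the same condition on newborn weight, so the condition is not peculiar to the Dubowitz score, and no other text provides for the smear. Even on the kinder reading, the wording of an endpoint's only data source needs repair.

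Other objections stand and limit the point:

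- A reader might infer that endpoint 10 would also have almost no data. The protocol does not support that. Every woman's gestation is assessed at entry, a home visit is timed from the birth, and mothers not seen by 6 weeks after the due date are visited at home. Preterm delivery can be derived without a Dubowitz score. What is missing is a statement that it will be.
- A reader might infer that a woman enrolled before about 33 weeks who delivers near day 28 must be preterm. That is too strong. Entry at 32 weeks puts day 28 at 36 weeks, and delivery one week later is at 37.
- Newborn weight is not a listed endpoint, so restricting it contradicts nothing in section 4.2.
- A reader might infer from endpoint 1 that foetal losses after dosing go unnoticed. They do not. Viability is checked at follow-up visits to day 28, foetal deaths go to the DSMB statistician (section 9), and section 11 pre-plans analyses of foetal viability and of birth outcome 6 weeks after the due date.

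**Conclusion.** The point holds for placental malaria. Read as printed, the schedule would yield about 1 to 8 placental smears per arm of 72, where about 50 to 58 are obtainable, and the few taken would over-represent preterm births. These counts rest on the assumed entry and delivery distributions and on a window the protocol leaves open. The conflict between endpoint 9, footnote d and the purpose of the 34-week limit does not depend on them.

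For preterm delivery the defect is smaller: a restricted supporting measurement and an unstated derivation.

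For foetal death it is a matter of wording. A loss after the treatment course but before the perinatal period is observed and reported, yet it falls outside endpoint 1 and outside the perinatal and neonatal mortality endpoint (7). That is a gap in the endpoint definition, not in surveillance.

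**What to change.** 1. Delete the day-28 condition from footnotes d and e of Appendix 1.
2. Take the placental smear and the newborn weight and maturity assessment at every study-hospital delivery, and list them in section 7(a).
3. State that preterm delivery is derived for all women from gestation at entry and date of birth.
4. Minor: reword endpoint 1 to match the foetal viability and birth outcome analyses in section 11, so that a loss after dosing but before the perinatal period is counted.

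The cost is modest: more smears to prepare and read and more newborn assessments, all of them procedures already in the schedule. The wording changes are confined to section 4.2, section 7 and Appendix 1. Women who deliver elsewhere would still have no placental result, so endpoint 9 should be reported as applying to hospital deliveries.

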## **Appendix 2 Extracts from SOPs.**

Quality control and assurance will be instituted through written standard operating procedures (SOPs) to assure that the trial is conducted and that data are generated, recorded, and reported in compliance with the protocol, good clinical practice (GCP), and the applicable regulatory requirements. Prior to enrolment, the clinical monitor and the PIs will review the protocol and all trial related procedures, information on the study regimens, procedures for obtaining informed consent, procedures for completing CRFs and for reporting AEs. The monitor will make regular visits, at which, information in the CRFs will be verified against the SD for accuracy and completion. Also, the monitor will review the informed consent procedure, drug accountability and storage, trial documents and trial progress. The clinical monitor will verify that the investigator follows the approved protocol and/or amendments (if any), and will discuss any problem/issue for improvement.

All women enrolled will be admitted to the research ward (to be built by the GMP) for the first three days for DOT and to monitor clinical response and adverse events. Patient demographic data and socioeconomic background will be collected. Clinical symptoms/signs and haematological profile will be recorded in a semi-structured enrolment form with a standardized checklist of symptoms and signs. At discharge, an identity card will be issued to facilitate follow up, prevent drug administration outside the study team and to exclude them from the study if they develop a second episode of malaria after completing the 28 day follow up.

Drugs will be administered orally by nurses employed by the project. After each administration, the patient will be observed for 45-60 minutes to ascertain drug retention. The dose will be repeated if vomiting occurs within the observation period, and any further vomiting will cause exit from study and treat with parenteral quinine.

If a patient is unable to tolerate the trial medication and treatment is discontinued, the reason for discontinuation will be recorded in the Clinical Record Form as “adverse event” and rescue medication initiated.

At study conclusion, the Clinical Monitor will return all unused medications to the sponsor, after a careful check and authorization.

Although the proposed study regimens are considered safe, there is need to look for any unlikely serious adverse event (SAE).

A SAE shall be reported within 24 hours by telephone, fax, or e-mail to the safety monitoring board. Thereafter, the PI will submit a written report describing the SAE, its onset, date of onset, type, duration, severity, cause-effect relationship to the administered drug(s), outcome and measures taken.

SAEs will be recorded in the CRFs, evaluated and discussed at the conclusion or termination of the study.

Personal data of patients will be kept confidential.

The agreement covering the use of data or analysis will be documented in writing together with the written informed consent for participation in the trial.

The PI will retain study material for an agreed period. Destruction of study material thereafter, will require a joint written authorization from interested parties.

All trial data will be recorded on the CRFs in English. Only the PI and a few authorized co-workers (as on the list of Authorized Signatory Form) will make entries.

Entries will be legible in black or blue ballpoint pen. Corrections should be made by drawing a single line through the original entry, entering the new value with initials and date next to the new entry. Completed CRFs will be dated and signed by the PI.

All clinical data will be entered into medical records. The clinical and laboratory results will be transcribed into the CRFs. SDs will be kept in a separate file from CRFs.

The clinical monitor will review all completed CRFs for completeness and accuracy before data entry into computer. Entry will have checks to identify errors and protocol violations. Request for clarifications and/or corrections on errors/violations will be sent to the PI. Analysis will be carried out after all queries have been addressed and database locked.

The PI will ensure that all study drugs are received, stored and documented. All study medications will be stored at room temperature under lock and key at the study site.

The PI will issue the study medications to the “dispensing nurse” of the study team. The dispensing nurse will account for all used and unused drug supplies. A drug accountability list will be kept in the investigator’s file. Remaining medications will be kept in the original blister packs. The nurse will keep blister packs with or without remaining drugs for inspection and validation against the drug accountability list

The PI will maintain a) a drug receipt form to confirm that supplies have been received b) a list of all drugs given to and returned by the dispensing nurse and c) a record of all unused drugs. Study drugs will only be used according to the study protocol; any discrepancy should be explained.

All personal demographic identification and clinical data/history will be recorded in the medical records to constitute the Source document (SD). The clinical data and laboratory results will be transcribed in the Clinical Report Form (CRF). The SDs and CRFs will be kept separately at the office of the PI.

The day of first treatment is day 0. Day 14-cure rate is the primary end point of therapeutic efficacy. It is the proportion of treated patients with no asexual parasitaemia on day 14, and who did not receive rescue medication.

An efficient medication should increase the haemoglobin level by at least 1 g/dl within 14-28 days of starting treatment, assuming no other causes for blood loss. To avoid group differences in taking iron/folate supplements, the study team will ensure that all participants receive standard routine care.

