**PROPOSED STARTING DATE: Nov 2003 DURATION: 2 years**

**1) SUMMARY**

Pregnant women are vulnerable to malaria, with significant implications both for their health and for the pregnancy. Sulfadoxine-pyrimethamine (SP) is currently the first line drug for the treatment of malaria in pregnancy in Tanzania and surrounding countries, but resistance is emerging rapidly. Alternative drugs must be found, and new drugs and drug combinations are being recommended by many for deployment as first line treatment at the point that SP resistance forces a policy change. However, there are few data on the safety and efficacy of these combinations in pregnant women. This randomised trial aims to assess efficacy and safety, including birth outcome, in pregnant women with malaria in the second or third trimesters. A total of 900 pregnant women will be randomised either to standard treatment (SP) or to one of three potential drugs, or drug combinations recently recommended by a WHO expert panel. These will be SP-amodiaquine, chlorproguanil-dapsone (Lapdap), and amodiaquine-artesunate. Primary outcome will be treatment failure at day 28. Secondary outcomes will include maternal side effects, foetal viability and birth outcome.

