### **4. TRIAL DESIGN**

#### **4.1 Primary end point**

The primary end-point of the trial will be treatment failure by day 28. This will be defined as:-

*Any of:-*

- 1) a need for rescue treatment due to clinical deterioration defined by altered sensorium, convulsions, persistent vomiting, renal impairment, respiratory distress, a fall in Hb below 7g/dl, or in cases where initial haemoglobin was less than 9 g/dl a drop of 20% from the starting Hb, at any time during admission;
- 2) persistence of fever with parasitaemia on day 3;
- 3) increasing parasite load on day 3;
- 4) failure to clear parasites on day 7;
- 5) rescue medication for recurrent malaria before day 28;
- 6) slide parasite positivity at day 28.

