*Based on the sample size of 80 women on SP alone and 240 in each of 3 combination regimens while allowing for 10% loss to follow up, a total of 900 women will be enrolled in the study. According to records at MCH for year 2000, a total of 6,880 pregnant women (approximately 20 per day) attended the antenatal clinic, of which an average of 6 per day had complaints. We assume that 3 of the sick 6 will have falciparum malaria and that 2 of them will consent to participate. Therefore, it will take 450 working days to enrol 900 women and the duration of the study is estimated to be 2 years.*

*The sample size should be adequate and sufficiently robust to detect common side effects in pregnancy. Rare side effects can only be detected in large Phase 4 and post-marketing surveillance studies. This study should provide information which can allow such studies to be undertaken.*

**Oct 2004.** Vigorous measures to protect pregnant women in the district from malaria on a general background of reduced transmission of malaria in this area have fortunately led to substantial reductions in the number attending the antenatal clinic with clinical malaria. The investigators reviewed the data from other sites, and it is clear there is still likely to be a critical shortage of data on antimalarials in pregnancy from Africa, so a trial even with an ability to detect this relatively large difference is likely to be of considerable utility to policymakers. A revised sample size has been calculated to detect a difference at day 28 from 1% (the best likely failure rate in any arm) and 15% (above which no drug could be deployed). This gives a sample size of 72 in each arm when  $\alpha$  was .05 and  $\beta$  0.8. This would be capable of detecting common, but not rare, adverse events. The trial will continue on this basis due to the public health importance of this question.

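### Appendix 2 names day-14 cure rate as the primary efficacy end point, contradicting the day-28 treatment failure endpoint that sections 1, 4.1 and 11 and both sample size calculations use

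*Protocol*

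**What the plan says.** Three places in the main protocol name the primary endpoint, and they agree on day 28.

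- Summary: "Primary outcome will be treatment failure at day 28".
- Section 4.1: "The primary end-point of the trial will be treatment failure by day 28". A list of six criteria follows, any one of which counts as failure; the last is "slide parasite positivity at day 28".
- Section 11, Data analysis: "Treatment failure as defined in section 4.1 is the primary outcome".

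The sample size section follows the same endpoint. The original calculation refers to treatment failure as section 4.1 defines it. The October 2004 revision says "A revised sample size has been calculated to detect a difference at day 28 from 1" per cent, set against 15%.

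Section 4.2 puts the day-14 parasite result among the secondary endpoints: "Parasite recrudescence or re-infection on day 14". Section 11 repeats it among the other pre-planned analyses.

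Near its end, Appendix 2 says otherwise: "Day 14-cure rate is the primary end point of therapeutic efficacy". It then gives that endpoint a definition of its own: "It is the proportion of treated patients with no asexual parasitaemia on day 14, and who did not receive rescue medication".

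**The concern.** One protocol carries two incompatible statements of its primary endpoint. Appendix 2 is part of the current document, not a record of superseded text, and the October 2004 modification, which re-sized the trial at day 28, left the sentence in place. There is no explicit clause saying which statement prevails.

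The definitions differ in time point and in content, so the same woman can be scored differently. Appendix 2 extracts the procedures by which data are to be recorded and reported. Someone working from that extract would therefore take day 14 as primary. The main analysis, and the failure rate policymakers read first, would then omit recurrences after day 14, and the sample size would have been justified for a different endpoint.

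**Working it through.** **1. The two definitions side by side**

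| Course of a woman | Section 4.1 (day 28) | Appendix 2 (day 14) |
|---|---|---|
| Clear on day 14, no rescue by then; recurrence with rescue before day 28, or positive slide on day 28 | Failure (criteria 5, 6) | Cure |
| Febrile with parasites on day 3, or parasites not cleared on day 7; handled as section 5.4 item 5 states | Failure (criteria 2, 4) | Not a cure, because rescue was given |
| Positive on day 14, no rescue, negative on day 28, no other criterion met | Not a failure on any listed criterion | Not a cure |

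The first row carries the point: it needs no departure from the plan, and the two definitions give opposite results. The third row is possible as written and runs in the other direction.

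**2. Which endpoint the sample size belongs to**

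Inputs from the October 2004 revision: p1 = 0.01, p2 = 0.15, alpha 0.05, 72 per arm. The 0.8 printed as beta is read as power. Sidedness is not stated; two-sided is assumed.

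Without continuity correction, with p̄ = (0.01 + 0.15)/2 = 0.08:

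n0 = [1.960·√(2·0.08·0.92) + 0.842·√(0.01·0.99 + 0.15·0.85)]² / 0.14² = [1.960·0.3837 + 0.842·0.3707]² / 0.0196 = 57.8, so 58.

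With continuity correction:

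n = (n0/4)·[1 + √(1 + 4/(n0·0.14))]² = 71.3, so 72. This is the stated figure.

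Power at 72 by the same formula: the effective size is m = 72·[1 − 1/(72·0.14)]² = 58.4. Then z = (0.14·√58.4 − 1.960·0.3837)/0.3707 = 0.858, which gives power 0.805.

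The stated 72 is therefore the continuity-corrected, two-sided number for 1% versus 15% at day 28.

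**3. Illustration for day 14**

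The protocol gives no day-14 rates for the revised calculation and no split of failures before and after day 14. Assumption: a share of one third to one half of day-28 failures appears after day 14, the same in both arms, and there are no day-14 failures outside the day-28 failures. Same formula, 72 per arm:

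| Share after day 14 | Day-14 failure rates | m | z | Power |
|---|---|---|---|---|
| None (day-28 design) | 1% vs 15% | 58.4 | 0.858 | 0.805 |
| One third | 0.67% vs 10% | 52.2 | 0.165 | 0.57 |
| One half | 0.5% vs 7.5% | 46.3 | −0.246 | 0.40 |

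The reduction must be applied to both arms. Shrinking only the 15% arm and keeping the comparator at 1% gives 0.52 and 0.33, which overstates the loss under this assumption.

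**The case against.** The strongest reply is that the intended endpoint is not in doubt. The Summary, sections 4.1 and 11 and both sample size calculations use day 28, and section 4.2 makes the day-14 parasite result secondary. Appendix 2 says its SOPs serve compliance with the protocol, which suggests they are subordinate to it. This largely stands. The sentence is probably a leftover, although the document does not say so, and a reader might wrongly infer that the trial has two primary or co-primary endpoints, or that the authors may freely choose between them afterwards. What the reply does not remove is a current statement that is wrong as written and has its own definition. Day 14 is also not foreign enough to the design to be dismissed at sight: the original sizing borrows day-14 rates, such as the 17% for amodiaquine, as inputs to a day-28 endpoint.

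Three stronger readings are tempting and are not supported.

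- *Day-3 and day-7 failures would be scored as cures under Appendix 2.* Section 5.4 item 5 states that women who fail receive rescue treatment, and Appendix 2 does not count rescued women as cured. If the plan is followed, both definitions score these women as not cured; they differ only after a protocol deviation.
- *Day 14 understates failure in every regimen.* That is likely where late recurrences are common, but the third row of the first table runs the other way, so it is not established for every arm.
- *A drug at the 15% ceiling would look deployable on its day-14 rate.* The protocol ties the 15% to day 28, so a day-14 rate is not measured against it.

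**Conclusion.** The contradiction is real and concerns the primary endpoint. It is one stray statement in Appendix 2 against an otherwise consistent day-28 design. Its substantive content is the recurrence on days 15 to 28, which the two definitions score in opposite ways. Only day-28 failure has a sample size basis, and that basis reproduces: 72 per arm, power about 80%, on a two-sided, continuity-corrected reading. If day 14 were taken as primary, the 72 would rest on no figure given for the revised calculation. The 57% to 40% power range shows only how far it could fall, and depends wholly on the assumed split of one third to one half, equal in both arms. The contradiction itself does not depend on that assumption.

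**What to change.** In Appendix 2, replace the statement that makes day-14 cure rate primary with a pointer to section 4.1. If the day-14 cure rate and its definition are kept, label it as a secondary endpoint and list it in section 4.2 beside the day-14 parasite result. Correct the underlying SOP in the same way, and do both before any analysis by arm.

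The cost is one amendment sentence and one SOP correction. Sample size, visits, blood smears and data collection stay as they are.
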